## Abstract

**Introduction:**

Wide variation in the management of key paediatric surgical conditions in the UK has likely resulted in outcomes for some children being worse than they could be. Consequently, it is important to reduce unwarranted variation. However, major barriers to this are the inability to detect differences between observed and expected hospital outcomes based on the casemix of the children they have treated, and the inability to detect variation in significant outcomes between hospitals. A stated-preference study has been designed to estimate the value key stakeholders place on different elements of the outcomes for a child with a surgical condition. This study proposes to develop a summary metric to determine what represents successful treatment of children with surgical conditions.

**Methods and analysis:**

Preferences from parents, individuals treated for surgical conditions as infants/children, healthcare professionals and members of the public will be elicited using paired comparisons and kaizen tasks. A descriptive framework consisting of seven attributes representing types of operations, infections treated in hospital, quality of life and survival was identified. An experimental design has been completed using a D-efficient design with overlap in three attributes and excluding implausible combinations. All participants will be presented with an additional choice task including a palliative scenario that will be used as an anchor. The survey will be administered online. Primary analysis will estimate a mixed multinomial logit model. A traffic light system to determine what combination of attributes and levels represent successful treatment will be created.

**Ethics and dissemination:**

Ethics approval to conduct this study has been obtained from the Medical Sciences Inter-Divisional Research Ethics Committee (IDREC) at the University of Oxford (R59631/RE001-05). We will disseminate all of our results in peer-review publications and scientific presentations. Findings will be additionally disseminated through relevant charities and support groups and professional organisations.

Strengths and limitations of this studyOur descriptive system has been developed using formative research best practice guidance.Our experimental design employs attribute level overlap and exclude implausible combinations of attribute and levels in the context of children with a surgical condition.All participants will complete a choice task paired comparison with one of the alternatives representing a palliative scenario that will be used as an anchor.Preference data from different stakeholders relevant to the decision context will be available to estimate the final summary metric.Given that children with surgical conditions are relatively few in number, data collection may present challenges, in particular for the identification of parents and healthcare professionals, which will be mitigated using a thorough recruitment strategy.

## Introduction

In England and Scotland, there are currently 24 Trusts/Health Boards commissioned to provide specialised surgery in children.^1^ Specialised surgery in children includes:

Management of rare surgical conditions in children.Provision of specified specialised surgical procedures during childhood.Surgery in neonates.Surgical management or procedures for more common paediatric surgical conditions when a child requires specialist preoperative, anaesthetic or postoperative care (simple surgical procedures in children with complex medical needs).

Many of the conditions falling under the remit of specialised surgery in children commissioning affect only a few hundred children in England and Scotland each year, and what little is known about these children’s long-term health and well-being suggests that even after treatment, they have significant ongoing healthcare needs.^2–8^ Widespread variation in the management of children with these conditions currently occurs,^2–7^ but due to the rarity of the conditions, it has not to date been possible to identify how much of this variation is unwarranted or associated with variation in outcome. To identify unwarranted variation in management and outcome between centres providing specialised surgery in children it is necessary to develop mechanisms that will:

Collect accurate, unbiased data about children treated in individual centres.Combine data from children with different conditions in a way that enables meaningful outcomes analysis.Enable adjustment for casemix factors affecting centres’ outcomes.

The NIHR-funded study ‘Improving unwarranted variation in outcomes of children’s surgery through a new Children’s Surgery Outcome Reporting system using routinely available data (CSOR)’ investigates whether one unified system is capable of addressing these three issues and therefore reducing unwarranted variation in surgical care. This protocol paper describes the study design of one of the CSOR sub-studies, tackling the second barrier.

The gold-standard approach for comparing outcomes of interest to patients with a specific condition is to use a core outcome set (COS).^9^ Several COSs have recently been developed that are relevant to children with a surgical condition.^10–13^ Development of these COSs has highlighted that while there are attributes of successful treatment that are unique to each individual condition, there are also attributes that are common across conditions. A single outcome measure that combines these common attributes with attributes that accurately reflected the condition specific elements of each COS (eg, a measure of quality of life) would be able to provide a meaningful assessment of how successful the treatment of a child with any surgical condition has been. The aim of this study is therefore to develop an algorithm to assist in combining these attributes into one summary metric, and therefore, determining what constitutes successful treatment of children with a surgical condition. This metric would facilitate combination of data from children with different conditions enabling meaningful outcomes analysis.

Whether a certain combination of common core outcomes across conditions indicates a successful or unsuccessful treatment depends on the value that relevant stakeholders place on the different elements of the core outcomes. Economists employ preference elicitation techniques to determine such values.^14^ Stated preference techniques such as discrete choice experiments (DCEs) are well suited to understand the value of potential combinations of core outcomes of paediatric surgery.^15^

A DCE is an experiment with choice tasks that elicit preferences indicating how individuals value attributes of alternatives in a decision scenario.^15^ The value of a scenario depends on the levels associated to attributes, which are the characteristics of health, treatments or healthcare services being evaluated.^15^ During a DCE, participants are presented with a number of scenarios and are asked to choose their preferred option, trading off among the attributes. DCEs can take different formats, but paired comparisons, where the participant is presented with two scenarios and asked to choose one, are most widely used.^16^ Other alternatives to paired comparisons exist including best-worst scaling and more recently kaizen tasks.^17 18^ Participants’ choices in stated preferences exercises are analysed using discrete choice models, where choices are associated with combinations of attributes and levels to understand participants’ preferences (ie, their relative importance).

This is a protocol for a stated-preference study designed to estimate the value key stakeholders place on different combinations of health and care outcomes following treatment of a child with a surgical condition. Stakeholders will be presented with a series of paired comparisons and novel kaizen tasks to elicit their preferences. The final product of the collected data will be an algorithm to determine whether the treatment of a child with a surgical condition has been ‘successful’ or ‘unsuccessful’. The use of stakeholder preferences to help in healthcare decision making by policymakers has increased considerably across most developed jurisdictions.^16^ This has been accompanied by best practice guidance for developing such studies, applied herein.^19–22^

### Aims

To understand how parents, guardians and healthcare professionals caring for children with a surgical condition, individuals treated for surgical conditions as children, and members of the general public value common health and care outcomes following treatment of a child with a surgical condition. Specifically:

- To estimate the relative importance of key health outcomes following treatment for a surgical condition in childhood for multiple conditions using a paired comparison and a novel kaizen task.

- To compare preferences between the two sources of preference data and type of participant in the context of children with a surgical condition.

- To estimate an algorithm using weights derived from the relative importance estimates to derive a summary metric that categorises outcomes following surgery in childhood into ‘successful’ or ‘unsuccessful’ outcome.

## Methods and analysis

### Overview of the framework for the stated-preference study

Figure 1 describes the framework and different phases that will be followed to conduct this study. This protocol describes the following sections: (1) identification and description, (2) experimental design, (3) survey instrument and (4) statistical evaluation.

**Figure 1 F1:**
[figure not shown]
A framework for stated-preference studies.

### Identification and description

#### Decision model and descriptive framework

We have followed the most recent guidance on formative research for the identification of attributes and levels for the descriptive system used in this study.^22^ Our decision problem explores how to best conceptualise what constitutes a more successful outcome following treatment for a surgical condition in childhood from the values that relevant stakeholders place on key core outcomes across paediatric surgical conditions. Our decision model hypothesises that a successful treatment for a child with a surgical condition can be represented by a combination of characteristics or attributes. In this study, we define attributes as core health outcomes included in available COSs relevant to paediatric surgery. The attributes and associated levels that describe potential outcomes following treatment define our descriptive framework. We used literature reviews, interviews with parents and paediatric surgeons, and group discussions with our Parent Advisory Group (PAG) to determine the descriptive system for the final survey instrument. Our PAG consists of over 100 parents and family of children who have undergone early surgery for conditions including Hirschsprung’s disease, gastroschisis, exomphalos, short bowel and necrotising enterocolitis.

An initial list of conceptual attributes were identified through a review of published COSs relevant to paediatric surgery. Relevant COSs have been developed for children with Hirschsprung’s disease, gastroschisis and appendicitis, as well as for children receiving neonatal care in a high-income setting.^10–13^ Each of these COSs was developed using a combination of literature reviews, an online Delphi process and consensus meetings, and included in their stakeholder groups, clinicians, allied health professionals, parents and children or adults previously treated for the target condition. We also conducted focused discussions with our PAG who had the opportunity to comment on the COSs identified in the literature review. The core outcomes identified in the above mentioned conditions are presented in table 1.

**Table 1 T1:** Summary of identified core outcomes in neonatal conditions

Category	Core outcome	Included in core outcome set?			
		Hirschsprung’s disease	Gastroschisis	Neonatal care	Appendicitis
Survival	Survival	x	x	x	x
Quality of life	Quality of life	x	x	x	x
	Psychological stress	x			x
	Time away from full activity				x
Adverse events	Unplanned reoperation	x			x
	No of operations		x		
	Severe gastrointestinal complication		x		
	Retinopathy of prematurity			x	
	Chronic lung disease			x	
	Bowel obstruction				x
	Readmission				x
	Length of hospital stay				x
	Significant infection		x	x	
	Hirschsprung’s associated enterocolitis	x			
	Necrotising enterocolitis			x	
	Wound infection				x
	Wound complication				x
	Intra-abdominal abscess				x
Condition specific	Faecal incontinence	x			
	Bowel function score	x			
	Voluntary bowel movements	x			
	Urinary incontinence	x			
	Permanent stoma	x			
	Growth		x		
	Time on parenteral nutrition		x		
	Liver disease		x		
	Brain injury on imaging			x	
	Motor/cognitive/visual/hearing ability			x	
	Antibiotic failure				x
	Negative appendicectomy				x
	Recurrent appendicitis				x

An iterative process to the identification of attributes was followed. In a first step, conducted by the clinical team (BA and MK), overlap in outcomes of importance was identified between the four COSs. Each COS also identified outcomes that were relevant only to the condition of interest, and not represented in the other COSs. In a second step, we reviewed these condition-specific outcomes with our PAG in order to determine how best to represent them in the descriptive system. The group concluded that these condition-specific outcomes were highly likely to impact the child’s overall quality of life and would therefore be adequately represented through an overarching attribute of quality of life. Three outcome categories, including survival, adverse events and quality of life, were common to all four relevant COSs and therefore selected as the initial set of attributes for the descriptive system. Similar outcomes have also been identified as important in other developed paediatric COSs.^23 24^ The specific adverse events identified from each COS were also discussed with our PAG and the CSOR paediatric surgeons in a group discussion. The PAG and surgeons agreed that the main adverse events were better summarised as operations, and hospitalisations due to significant infections. Therefore, four core attributes were identified at the end of the second step. A description of each attribute is given next:

##### Operations

Most surgical conditions are treated with one or more operations. Some operations that a child might undergo will be planned at the beginning of the child’s treatment, while some will be emergency, or unplanned operations. The complexity of each operation also varies, from minor operations, such as draining an abscess, to more major operations, such as removing sections of intestine (bowel or gut). For the purpose of the preference study, the number of operations will be presented within four different attributes according to type of operation.

##### Whether the child has an infection treated in hospital after their operation

Each of the COSs identified as relevant to paediatric surgery include condition-specific significant infective complications, such as enterocolitis and intra-abdominal abscess. Some also include a more generalised measure of significant infection, sepsis. For the purposes of the preference study, the infective complications included in each COS will be represented by the attribute infections treated in hospital, and the levels will define the frequency of infections.

##### The child’s quality of life

Each of the COSs included the outcome quality of life, while some also specifically included outcomes relating to psychological well-being. There are multiple instruments to measure quality of life in children, but they have not been validated in children with a surgical condition. These tools generally describe multiple domains, including social functioning, physical functioning and psychological well-being, with their output generally reported in a continuous manner. However, for the purposes of our descriptive system, quality of life will be categorised as good, fair or poor. The impact of key condition-specific outcomes will be reflected in the child’s overall quality of life.

##### How long the child survives after their diagnosis

Although death is relatively uncommon following most surgery in childhood, it is such a significant outcome that all four COSs relating directly to childhood surgery, and the majority of paediatric COSs include it. For the purposes of the descriptive system, this outcome will be presented positively as survival.

The identification of the attribute levels also employed an iterative process. First, we reviewed the epidemiological data available for each of the attributes to guide the range that could be presented to participants. Existing large-scale cohort studies describing the outcomes for children with a range of conditions treated under the specialised surgery in children commissioning, and affecting different regions of the body, modes of presentation and urgencies of intervention were reviewed.^2 4–6 8 25–33^ A researcher (BA) extracted point estimates and associated measures of uncertainty for each of the attributes. In discussions with two other researchers ([name] and [name]) initial deterministic ordinal levels for each attribute were developed. The selection of levels considered the potential participant cognitive burden and the ability to test appropriate functional forms hypothesis (eg, linear, quadratic) for quantitative attributes. This initial list of ordinal levels was discussed with paediatric surgeons in a group meeting to ensure their clinical appropriateness and also suggested changes to the wording. The language used to describe the levels was refined further following review by members of the PAG. Finally, we conducted three think aloud exercises with different parents who completed a mock choice task of the survey instrument with two of the researchers ([name] and JB). Parents were given the opportunity during these interviews to comment on the wording used for the attributes and associated levels. The proposed attributes and attribute levels are described in the descriptive framework in table 2.

**Table 2 T2:** Study descriptive framework

Attributes	Attribute levels
Planned major operations related to the condition	No planned major operations One planned major operation Two planned major operations Six planned major operations
Planned minor operations related to the condition	No planned minor operations One planned minor operation Two planned minor operations Six planned minor operations
Emergency major operations related to the condition	No emergency major operations One emergency major operation Two emergency major operations Six emergency major operations
Emergency minor operations related to the condition	No emergency minor operations One emergency minor operation Two emergency minor operations Six emergency minor operations
Infections treated in hospital	No infections treated in hospital One infection treated in hospital Two infections treated in hospital Six infections treated in hospital
Child’s quality of life	Good quality of life Fair quality of life Poor quality of life
How long the child survived after their diagnosis	More than 20 years, without any expectation that their surgical condition would shorten their life expectancy 20 years 5 years 1 year 6 months 1 month

#### Elicitation task and format

Two elicitation formats will be used in this study to estimate preferences: a paired comparison and a kaizen task. Each paired comparison will include two scenarios describing combinations of treatment outcomes of a child with a surgical condition without an opt-out option. An example is presented in online supplemental material 1. This type of choice task is the most widely used format in health preference research^16^ and has been used previously to elicit preferences for outcomes of surgery.^34–36^

10.1136/bmjopen-2022-062833.supp1Supplementary data

Recent work has reported that valuation can be problematic in the context of child health.^37 38^ Eliciting values to inform decision making at the start of life or early childhood requires stakeholders to complete tasks from someone else’s point of view. There is some evidence that when the tasks in an elicitation exercise refer to someone else’s instead of their own preferences, individuals find the exercise strenuous. This is accentuated when the perspective is that of a newborn babies or a young individual.^37^ In a paired comparison, it is easy to understand that choosing between two undesirable outcomes of paediatric surgery could be distressing to stakeholders. Moreover, members of the general public may find it both distressing and unfamiliar as they find it difficult to relate to the decision context.^39^ This in turn can affect the preferences elicited in paired comparisons.

In addition to the paired comparisons in this study, we will therefore also administer a series of kaizen tasks to participants (online supplemental information 1). Each kaizen task begins with a paired comparison between a single profile and a palliative one (ie, no operations and no infections, but the child has fair quality of life and dies within 1 month). Next, the respondent makes three improvements to the single profiles. After these improvements, the respondent completes a final paired comparison between the improved profile and a palliative one. Respondents may find the task of improving a child’s health to be more engaging than choosing between two diverse outcomes.

### Experimental design

A preliminary experimental design has been completed for both elicitation exercises using a three-step approach: (1) generation of a design for the paired comparison task and (2) selection of pairs for the first and third part of the kaizen task and (3) selection of profiles for the second part of the kaizen task.

Our preliminary design has employed a D-efficient design to identify the combination of pairs to present in the paired comparison.^15^ This is a procedure for generating choice tasks (for respondents) in a way that maximises the statistical efficiency of the choice models that will be estimated. Several restrictions were imposed including ‘overlaps’ in three attributes to reduce cognitive burden (similar attribute levels between pairs) and implausible combinations of outcomes. These combinations were identified by the CSOR surgical team and included:

Reject scenarios in which quality of life is good, the child survived for less than 1 year, and the child underwent 20 or more operations.Reject scenarios in which the child underwent any number of minor operations, but no major operations, and survived for less than 20 years.Reject scenarios in which the child underwent fewer than six minor operations, no major operations, and quality of life is low.Reject scenarios in which quality of life is good, the child survived for less than 6 months, and the child underwent any major operations.

A candidate set was created including these restrictions and used as the initial candidates in Ngene.^40^ We generated a preliminary design with 45 choice tasks divided into five blocks to which participants will be randomly allocated that is, nine choice tasks in each block. Participants will be randomised to one of these five blocks and the order of the pair in each choice task will also be randomised.

An additional choice task was added to all blocks, which serves as an ‘anchor’. This anchor was a palliative profile defined as having no operations, no infections, fair quality of life and a survival of 1 month. This anchor will be used to facilitate comparisons between paired comparison and kaizen responses and also when developing the final algorithm for CSOR. The experimental design is presented in online supplemental material 2.

10.1136/bmjopen-2022-062833.supp2Supplementary data

The experimental design for the kaizen task was constructed directly from the pairs in online supplemental material 2. Given each pair, an initial profile of the kaizen task was constructed from the worst attributes found in the pair. Likewise, the four possible improvements were defined to be the best attributes found in the pair. Therefore, the preference path captured by the kaizen task should agree with the paired comparison response (ie, the path passes through profile chosen in the paired comparison before passing through the profile not chosen in the paired comparison).

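### The kaizen construction does not carry over the study's own plausibility rules, so recombined profiles need a separate screen

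*Protocol article*

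**What the plan says.** The Experimental design section of the protocol article lists four combinations that the surgical team judged implausible. One of them reads: "Reject scenarios in which the child underwent any number of minor operations, but no major operations, and survived for less than 20 years". The rules enter the design at one stated point: "A candidate set was created including these restrictions and used as the initial candidates in Ngene". A further constraint is set on each pair: "Several restrictions were imposed including ‘overlaps’ in three attributes to reduce cognitive burden".

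The kaizen tasks are then derived from the resulting pairs: "The experimental design for the kaizen task was constructed directly from the pairs in online supplemental material 2". The article states that "an initial profile of the kaizen task was constructed from the worst attributes found in the pair", and that "the four possible improvements were defined to be the best attributes found in the pair". The Elicitation task and format section adds: "Next, the respondent makes three improvements to the single profiles". The respondent compares the start, and later the improved profile, with the palliative one.

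The Strengths and limitations list says that the experimental design uses overlap and will "exclude implausible combinations of attribute and levels".

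**The concern.** Each rule rejects a combination of levels, not a single level. Taking some levels from one permitted profile and some from another therefore gives no assurance that the mixture is permitted. The kaizen task does exactly this, at the start and again at each improvement. The respondent chooses the order, so screening the start alone would not prevent it.

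Aim 2 and the Data analysis section compare preferences between the two elicitation formats, and the kaizen coefficients are candidates for the final algorithm. If some kaizen tasks rest on profiles that the surgical team called implausible, while no paired comparison does, format and plausibility are partly mixed in that comparison.

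**Working it through.** **Inputs.** Levels are from Table 2: five attributes with four levels (0, 1, 2, 6), quality of life with three, survival with six. The rules, the overlap and the 45 pairs are from Experimental design. Readings assumed: low quality of life means poor in Table 2; planned and emergency counts are added; overlap means exactly three equal attributes; in rule 2, any number of minor operations means one or more. The last reading fits the protocol's own palliative profile (no operations, 1 month), which rule 2 would otherwise reject.

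**The plan's own figure.** 7 attributes − 3 overlapping = 4 that differ, which agrees with the four improvements stated.

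**Permitted profiles.** There are 4^5 × 3 × 6 = 18,432 profiles.
- Rule 1 (good quality of life, under 1 year, at least 20 operations): 5 operation patterns × 4 infection levels × 2 survival levels = 40.
- Rule 2 (minor but no major operations, under 20 years): 15 × 4 × 3 × 4 = 720.
- Rule 3 (no major, fewer than six minor, poor quality of life): 9 × 4 × 6 = 216.
- Rule 4 (good quality of life, under 6 months, any major): 15 × 16 × 4 = 960.
- Counted twice: rules 1 and 4, 5 × 4 = 20; rules 2 and 3, 8 × 4 × 4 = 128.

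Rejected: 40 + 720 + 216 + 960 − 148 = 1,788. Permitted: 18,432 − 1,788 = 16,644.

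**Example 1, a rejected profile on the path.**
- A: no operations, no infections, fair quality of life, 5 years. Permitted.
- B: two planned major, one planned minor, no infections, good quality of life, 20 years. Permitted.
- Emergency major, emergency minor and infections are equal, so three attributes overlap.
- Start: two major, one minor, fair, 5 years. Permitted.
- Improving planned major operations first leaves one minor, no major, 5 years. Rule 2 rejects this.

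In random order the path meets a rejected profile if major operations come first (1/4), or quality of life first and major operations second (1/4 × 1/3 = 1/12): 1/3 in all. No final profile is rejected in this example.

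**Example 2, a rejected final profile.**
- A: no operations, two infections, fair, 1 year. B: one planned major, no infections, poor, 5 years. Both are permitted.
- If quality of life is the attribute left unimproved (1/4 in random order), the final profile is no operations, no infections, poor, 5 years. Rule 3 rejects it, and it is the profile set against the palliative one.

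**Example 3, a rejected start.**
- A: no operations, two infections, good, 1 month. B: one planned and one emergency major, no infections, good, 5 years. Both are permitted.
- Start: two major, two infections, good, 1 month. Rule 4 rejects it.

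**All permitted pairs.** Exact enumeration of pairs that differ in exactly four attributes, both profiles permitted and neither dominating, gives 21,053,280 pairs. For each, the start and the 14 profiles reachable with one to three improvements were checked.
- Rejected start: 107,684 / 21,053,280 = 0.5%.
- At least one rejected start or reachable profile: 2,001,338 / 21,053,280 = 9.5%. All four rules occur.
- At least one possible final profile rejected: 1,762,782 / 21,053,280 = 8.4%.
- Improvements in random order: 4.6% of tasks pass through a rejected profile and 3.3% have a rejected start or final profile. A separate simulation of 60,000 such pairs gave about 4.5% and 3.2%.
- With dominated pairs included, the first three shares are 0.4%, 9.9% and 8.8%.
- If rule 2 also covers zero minor operations, examples 1 to 3 fall away because A is then rejected in each, but 9.3% of pairs still have a rejected start or reachable profile.

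**After screening.** 21,053,280 − 2,001,338 = 19,051,942 pairs remain, or 90.5%.

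**The case against.** The strongest reply is that the article never says the recombined profiles went unchecked. It names selection of pairs and of profiles as steps in the kaizen design. Each block has nine design pairs while a respondent sees three kaizen tasks, so some selection presumably took place on criteria that the article does not give. A condensed article may omit a screening step. This stands: the absence of a check is an inference, and the point is confined to the construction as stated.

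It is also fair that the percentages do not describe this study. A D-efficient design is not a random draw from the permitted pairs. A reader might multiply up, 1 − (1 − 0.095)^3 = 26%, and conclude that about a quarter of respondents meet an implausible profile. The documents do not support that. It treats the three tasks as independent random pairs, and it counts profiles that could be reached, not those that are. Even on random pairs, the matching figures for random order are about 13% for any profile on the path and about 9% for the start or final profile, which are the ones judged against the palliative scenario.

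A reader might also infer that the format comparison is biased, or that the stated strength is contradicted. Counting rule violations shows neither. No effect on coefficients has been estimated, and the statement about exclusion can be read as describing the paired-comparison design, for which it holds.

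What the reply does not remove is the logical gap: the stated construction does not by itself keep kaizen profiles within the rules.

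**Conclusion.** The concern holds in a limited form. Recombining levels from a permitted pair can produce start, intermediate and final kaizen profiles that the study's own rules reject. The worst-level start is the small part (about 0.5% of permitted pairs); most of the problem arises along the improvement path (about 9.5%). The result rests on the readings listed above and on weighting all permitted pairs equally. Whether any of the actual 45 pairs is affected cannot be determined without the supplement. If some are, the comparison of formats under aim 2 could be distorted, with direction and size unknown. As described, exclusion of implausible combinations is guaranteed only for the paired comparisons. This is an inexpensive improvement to the design, not a demonstrated error in its results.

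**What to change.** Before launch, list for each candidate kaizen pair the start profile and every profile reachable with one, two or three improvements (1 + 4 + 6 + 4 = 15 profiles). Apply the same four rules, and use for kaizen only pairs with no rejected profile. State in the article or supplement that this was done; if it has been done already, one sentence closes the point. If data have been collected, flag the affected tasks and repeat the between-format comparison without them.

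The cost is a short filter run on the existing design and the loss of a few pairs for kaizen use; the paired comparisons are untouched. If kaizen tasks follow the five blocks, which the article does not say, 3 × 5 = 15 passing pairs out of 45 would be enough, provided each block keeps at least three.
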